#### Power analysis and effect sizes

A series of simulation studies were performed to investigate power of the planned evaluation study [41]. A logistic regression model was used to randomly generate data corresponding to the assumed percentage of patients satisfying each ABCS criterion prior to and after the implementation support period as specified in Table 3. The model was specified according to the mean model introduced by Hussey and Hughes [42] and included a random effect corresponding to practice (the unit of randomization), a fixed implementation support effect where the implementation support covariate was modeled using a fractional covariate of (0.25, 0.5, 0.75, and 1.0) for the 3, 6, 9 and 12-month post-initiation practice performance measures to account for an implementation support strategy that is not fully effective until the 12-month time point following initiation. Note that for half of the practices, the fractional covariate is delayed by an additional 6 months relative to the Series implementation scheme given that one pair of targets (blood pressure/smoking or aspirin/cholesterol) is delayed by 6 months in each practice. The model also included a random error term. The correlation among measures made on patients from the same practice was assumed to be 0.10 or less [43]. After the data were generated, Generalized Estimating Equations (GEE) methodology was used to fit a logistic regression model to test the significance of the implementation support strategy effect. The percentage of simulated data sets that resulted in a significant intervention effect was recorded as the power of the specified study design. The power analysis assumes a 2-sided 0.05 alpha level. For each ABCS endpoint, 500 simulated data sets were generated. Estimated power is summarized for each target in Table 3. The power of the implemented analyses will be higher than that from the simulation studies, given that all active patients in the targeted clinical population for a particular ABCS criterion during a 3-month period will be analyzed per practice unit.

**Table 3 Tab3:** Summary of the assumed intervention effect sizes and power

Endpoint	Patient Cohort Characteristics (defining cohort eligible for intervention)	Baseline^a^ Percentage	Post-intervention Percentage	Power
A: Aspirin (aspirin or other antithrombotic prescribed)	Aged 18 years and older with ischemic vascular disease without a contraindication to aspirin	60%	70%	> 95%
B1: Blood Pressure Management 1 (blood pressure adequately controlled)	Aged 18–85 who had a diagnosis of hypertension	65%	70%	> 95%
B2: Blood Pressure Management 2 (blood pressure adequately controlled as per co-morbidity-adjusted targets)	Aged 18–85 who had a diagnosis of hypertension	65%	70%	> 95%
C1: Cholesterol Management 1:** (fasting LDL test AND ≤ LDL goal)	Aged 20–79	15%	25%	> 95%
C2: Cholesterol Management 2:** (fasting LDL test AND prescribed statin if indicated)	Aged 20–79	15%	25%	> 95%
S: Smoking cessation support (screening about tobacco AND received cessation counseling if tobacco user)	Aged 18 years and older	60%	70%	> 95%

^a^Estimates for the baseline percentages for aspirin use, blood pressure management, and smoking cessation support are based on Oklahoma Foundation for Medical Quality (OFMQ) primary care practice initiatives in the state of Oklahoma

^**^The C1 and C2 measures were calculated as the product of the probability of having a fasting LDL test (estimated to be 0.3) multiplied by the probability of having an LDL measure below the target (estimated to be 0.50) or being prescribed a statin if indicated (estimated to be 0.5) conditional on having a fasting LDL test

*Abbreviation*: *LDL* low-density lipoprotein

Practices drop out of QI projects when there is a significant disruption in the practice’s internal (e.g., significant clinician or staff turnover, new EHR) or external (e.g., new ownership) environment. On average, we have experienced a drop-out rate of about 5% during a 6-month initiative from previous experience. We therefore estimated a 10% drop-out rate in this 1-year project. Among the 263 recruited practices, we expect to retain at least 234 practices for the entire duration of the 3-year evaluation program.

#### Analytic plan

The evaluation plan has 2 analytic goals: (1) determine the impact of the implementation support strategy on the practice’s capacity to change, performance indicators and patient outcomes; and (2) assess the role of internal and external contextual factors and intervention characteristics on the uptake of the implementation support strategy and on practice performance and outcomes.Impact of the implementation support strategy on the practice’s capacity to change, performance indicators and patient outcomes

The effect of the implementation support strategy on the mean capacity to change score (priority for improvement, change capacity, and care process content), or the log odds of dichotomous indicators of change, will be estimated using GEE to fit linear and logistic regression models, respectively, based on a within-cluster and between-cluster analysis [42]. As discussed by Hussey and Hughes [42], GEE has several attractive properties that are relevant to the analysis of data arising from stepped wedge designs, including accommodating generalized linear models that are appropriate for continuous, count and dichotomous outcome measures, as well as robustness to variance and covariance misspecification. The small sample limitations of GEE-based estimation will not be of concern in this study given that 263 practices will serve as the unit of randomization and 11 time points will be utilized in the design. The outcome variable will be a continuous score measure or a Yes/No indicator variable measures at a practice unit level. The exposure of interest will be a dummy variable indicating the implementation support strategy exposure, which will be coded according to the randomized assignment (intent-to-treat analysis). Practice unit-level data will be analyzed where the nested clustering of practice units nested within practices, nested within sub-regions will be accounted for using a structured working correlation structure [44]. Cluster sizes, by county, will vary due to the targeted sampling of metro counties (25 practices per county) and more rural counties (one to five practices per county) and therefore, a jackknife estimate of the variance will be used to maintain the size of the test [42]. The time since the initiation of the implementation support strategy will also be considered as an independent factor in the regression model, along with a time by implementation support strategy interaction, to investigate the effect of the implementation support strategy relative to the time since initiation (i.e., delayed treatment effect). If a significant time by implementation support strategy effect is found, the analyses will be stratified by time period to estimate the time-specific implementation support strategy effect. Time-varying secular trends will be considered in the model, including the implementation of other health intervention programs in the studied sub-regions. Geographic region will also be considered as a modifying factor where region is fit as a series of four indicator variables (indicator for each quadrant, with the combined Tulsa and Oklahoma City metro areas serving as the reference group). If appropriate based on estimates, a dichotomous region variable indicating metro versus non-metro locations will be considered. A Type III Wald statistic will be used to determine the overall significance of the interaction between implementation support strategy and the five degrees of freedom categorical class variable for region. A 2-sided 0.05 alpha level will be used to define statistical significance. An intention-to-treat paradigm will be followed where data from all practice units are analyzed according to the randomized assignment regardless of adherence or implementation quality.

Logistic regression models will be fit to estimate the effect of the implementation support strategy on the log odds of attaining an ABCS criterion for a given patient. The outcome variable will be a Yes/No indication of attaining an ABCS criterion measured at a patient level. Individual-level data will be analyzed where the nested clustering of patients within practice units, nested within practices and counties will be accounted for using a structured working correlation structure [44].

Poisson regression models, with a log link, will be used to estimate the effect of the implementation support strategy on the incidence rate of patient outcomes, (ED visits, preventable hospitalizations, heart attacks, strokes, GI bleeds, deaths, etc.), where practice unit data are summarized for each 3-month time period. The outcome will be the number of patient events reported among the active adult patients in a practice unit and the offset will be the total number of patient-months of time at risk during the 3-month time period for the practice unit. GEE will be used to account for the correlation among nested practice units within practices within counties and modifying factors will be investigated.(2)Role of internal and external contextual factors and intervention characteristics on the uptake of the implementation support strategy and on practice performance and outcomes.

General regression modeling strategies described by Baron and Kenny [45] will be used to investigate modifying and mediating factors, as presented in the Logic Model, controlling for clustering. In brief, factors that modify the effect of the implementation support strategy will be indicated by significant interaction terms in the regression model. For example, organizational contextual factor scores will be investigated as modifying factors to determine if there is evidence that the effect of the implementation support strategy is greater among those practice units that have higher scores on the contextual factors. Mediating variables will be investigated by fitting a series of four regression models. First, the effect of the implementation support strategy on the health outcome measure will be estimated. Second, the association between the implementation support strategy (independent factor) and the potential mediating factor (outcome) will be estimated. Third, the association between the mediating factor (independent factor) and the health outcome variable will be estimated. Finally, the model will be refit to include the implementation support strategy and mediating term as independent factors with the health outcome measure modeled as the outcome variable. A change in the implementation support strategy coefficient, indicating a shift towards no effect on the outcome, with adjustment for the mediating factor will provide evidence of a mediating association.

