#### Evaluation design

A stepped-wedge cluster randomized trial design was used to evaluate the program. ABCS outcomes would be evaluated every 3 months beginning in month 7 of the project following an initial 6-month period for recruitment of the practices and practice units within each county, validation of the HIE data, and development of computing code for data abstraction from the HIE system. ABCS performance will be evaluated at each of the 263 practices during each 3-month period where the time of initiation of implementation support is randomly assigned. Each of 20 PFs were assigned to geographic sub-regions, nested within the five geographic sectors, in the state. The sub-regions reflected collections of counties that were feasible to access by a given PF. Within each sub-region, the consenting practices were randomly assigned to begin the intervention program in Wave 1, 2, 3, or 4 (Fig. 4). The targeted randomization was a total of 13 randomized practices per PF with three to four practices initiating the intervention program per Wave per PF. Random assignments were made in a manner to ensure a balance of Wave assignments for each PF and sub-region. In addition, during the 12-month implementation support period, two of the four programs were introduced in each 6-month period, where blood pressure management and smoking cessation support were introduced together and aspirin use and cholesterol management were introduced together. Within each of the four Waves, half of the counties introduced blood pressure management and smoking cessation support first and the other half introduced aspirin use and cholesterol management first, where the order assignment was randomly determined to ensure a balance by PF sub-region. The randomization sequences were generated using random number generation in Excel.

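### The GEE large-sample claim rests on 263 practices although the plan's own top-level clusters are about 20 sub-regions in one model and 75 county units in the others, and four region indicators are given five degrees of freedom

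*Protocol article*

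**What the plan says.** All references are to the protocol article.

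- **Basis for large-sample inference (Analytic plan).** The text says that "small sample limitations of GEE-based estimation will not be of concern in this study given that 263 practices will serve as the unit" (meaning the unit that is randomized). The 11 time points are given as a further reason.
- **Top level, capacity-to-change models (Analytic plan).** Clustering of "practice units nested within practices, nested within sub-regions will be accounted for using a structured working correlation structure". A jackknife variance is planned to hold the test size. The reason given is that the number of practices per county varies.
- **Top level, ABCS models (Analytic plan).** "nested clustering of patients within practice units, nested within practices and counties will be accounted for". The Poisson models for patient events also stop at counties. Neither mentions the sub-region.
- **Delivery and randomization (Evaluation design).** "Each of 20 PFs were assigned to geographic sub-regions, nested within the five geographic sectors, in the state". The target was "a total of 13 randomized practices per PF with three to four practices initiating the intervention program per Wave per PF". Practices were randomized to waves within sub-region, with balance by PF and sub-region.
- **Number of counties (Sampling methods).** 75 counties or paired county units.
- **Region interaction (Analytic plan).** First "region is fit as a series of four indicator variables", with the two metro areas combined as reference; then a Type III Wald test with "the five degrees of freedom categorical class variable for region".

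**The concern.** A GEE sandwich variance adds up contributions from clusters taken as independent, so its large-sample behaviour depends on how many such clusters there are. Randomized units inside a cluster, or repeated measurements, do not raise that number. If practices are correlated within sub-regions, as the capacity model assumes, 263 is the wrong count for judging small-sample limits.

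The choice of top level also decides which variation the standard error carries. A PF delivers the support to all practices in an area, and the Practice facilitation section itself calls the PF's relationships with the practice critical to effectiveness. A support effect that differs between PFs is therefore plausible. Practice or county clustering does not fully carry that variation.

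For region, the degrees of freedom set the critical value of the interaction test. Four indicators and five df cannot both be right.

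**Working it through.** **1. Cluster counts from the plan's own figures**

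- Randomized practices: 263.
- County units: 75.
- PFs: 20. At 13 practices each, 20 x 13 = 260; actual 263 / 20 = 13.15. One sub-region per PF gives about 20 sub-regions. The article does not count them, so this is an assumption.

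**2. What the count does to a z reference**

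If the true reference is t on (clusters minus 1) df, the size of a nominal 5% z test is P(|t| > 1.96):

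| Top level | Clusters | df | True size |
|---|---|---|---|
| Practice | 263 | 262 | 5.1% |
| County unit | 75 | 74 | 5.4% |
| Sub-region | 20 | 19 | 6.5% |

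The stated reassurance is right for 263 or 75 independent clusters, but not for 20.

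**3. Null simulation of the support-effect test**

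From the article: 263 practices, 20 sub-regions (as read above), 75 county units, 11 periods, 4 waves balanced within sub-region. Assumed: continuous cell means in place of binary data, practice SD 1, cell SD 0.7, an on/off exposure, and waves one or two quarters apart (the design figure is not shown). There were 1,000 runs per case, so the Monte Carlo SE is sqrt(0.05 x 0.95 / 1000) = 0.7 points. Entries are rejection rates in percent, for one- / two-quarter spacing.

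| Sub-region variation assumed | Practice, sandwich z | County, sandwich z | Sub-region, sandwich z | Sub-region, jackknife t(19) |
|---|---|---|---|---|
| None | 4.9 / 5.4 | 4.9 / 6.1 | 6.9 / 7.8 | 4.5 / 5.3 |
| Level, SD 0.7 | 6.2 / 6.0 | 6.9 / 6.5 | 8.7 / 8.7 | 6.9 / 5.7 |
| Level and period, SD 0.5 each | 1.7 / 2.3 | 2.5 / 2.9 | 6.6 / 6.1 | 4.8 / 4.0 |
| Support effect, SD 0.15, mean 0 | 7.8 / 11.4 | 7.6 / 10.5 | 7.3 / 7.5 | 5.0 / 6.0 |
| Support effect, SD 0.30, mean 0 | 17.4 / 23.0 | 14.8 / 17.0 | 7.9 / 7.7 | 6.0 / 5.0 |

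The last two rows also carry a sub-region level with SD 0.5. A jackknife by practice or county does not remove the inflation there: 7.5-22.3% by practice and 7.0-15.5% by county.

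A second simulation used 20 x 13 practices, 11 quarters, ICC 0.10, 20-100 patients per quarter and 800 runs per cell. By sub-region it gave 6.5-7.6% for sandwich with z, 6-7% for jackknife with z, and about 5% for jackknife with t(19). By practice, with an assumed PF-effect SD of 2-3 percentage points, it gave 5-16%.

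**4. Region degrees of freedom**

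There are four quadrants plus one combined metro reference, so five levels. The interaction with a single exposure column has 5 - 1 = 4 df; the stated five does not reproduce. It would need the metro areas kept apart (4 + 2 = 6 levels, 5 df), but the text combines them.

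- 95% limits: chi-square 4 df, 9.49; 5 df, 11.07.
- Size if a 4-df statistic is held to 11.07: P(chi-square on 4 df > 11.07) = 2.6%.
- Power: a noncentrality of 11.94 gives 80% at 9.49 and 72% at 11.07.

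**The case against.** The strongest reply is that the main test is protected by design. Waves were randomized by practice and balanced within sub-region, so a shared sub-region level or time trend affects all waves in it alike. The simulation bears this out: with practice or county clustering the first three rows run from 1.7% to 6.9%. A reader might infer that the plan's test sizes are simply wrong. The documents do not support that. Clear inflation from leaving out the sub-region needs a support effect that varies between PFs, and the article gives no figure for it. If the target is the average effect over these PFs only, even that variation need not enter the standard error. The article does not say so, and its stated aim of guiding future dissemination points the other way.

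Next, a jackknife is already planned to hold the size. This stands. The article may leave the deleted unit and the reference distribution to a fuller plan, so their absence is not the point. They matter here because the one reason given for the jackknife is unequal county size, and a county jackknife would not cover PF-to-PF variation.

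Third, 20 sub-regions is an inference. A metro county with 25 practices, against a target of 13 per PF, may be split between PFs, so neither the count nor clean nesting of counties is certain. This stands. The simulations also mimic quarterly outcome data, whereas the capacity scores come from surveys at three time points. For that model the 6.5% in step 2 is the more direct guide.

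Fourth, software would normally assign 4 df, so the region slip may be wording only. That is likely, but the text contradicts itself either way.

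A reader might also infer that five sectors made of 4 quadrants and 2 metro areas is a miscount. It is not: 4 x 50 + 2 x 25 = 250, and the metro pair forms the fifth sector of 50.

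**Conclusion.** The point holds as an inconsistency in the stated basis of inference, not as proof that the main test is invalid.

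- **GEE claim.** The count of 263 does not fit sub-region clustering. With about 20 clusters, sandwich with z runs at about 6-9% and jackknife with t(19) at about 4-7%.
- **Top level.** It changes from sub-region to county without explanation, and the randomization stratum drops out of the ABCS and Poisson models. The consequence is near nil or conservative if PFs do not differ in effect. If they do, the size may exceed nominal by an amount the documents cannot fix: 5-23% across the two simulations under assumed variances.
- **Region test.** It has 4 df. Read literally, five df makes a secondary test conservative (2.6%) and costs it power; the main effect test is untouched.

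These figures assume one sub-region per PF, the variance components and wave spacings listed, and continuous cell means.

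**What to change.** 1. Include the PF sub-region as a stratum in the capacity, ABCS and Poisson models, and use it as the top-level cluster in all three. State how many sub-regions there are and whether any county is split between them.
2. Apply the planned jackknife by leaving out one sub-region at a time, with a t reference on (number of sub-regions minus 1) df. Permuting wave within sub-region is an alternative; it tests for no effect in any practice, so it does not address variation between PFs.
3. Delete the sentence on small-sample limits, or rest it on the number of top-level clusters.
4. Change five degrees of freedom to four for the region interaction.

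Cost: wording and code, no new data. Intervals widen by about 7% from the t reference (2.09 / 1.96 = 1.07 with 20 sub-regions), and by more if PF effects truly vary, because the standard error would then carry that variation.

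### The 0/1 exposure dummy named for analysis does not match the delayed 12-month ramp behind the >95% power, and no ABCS exposure term or start date is fixed

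*Protocol article*

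**What the plan says.** Power (Power analysis and effect sizes). "The model was specified according to the mean model introduced by Hussey and Hughes". The support effect was "modeled using a fractional covariate of (0.25, 0.5, 0.75, and 1.0) for the 3, 6, 9 and 12-month post-initiation practice performance measures". The section adds that "for half of the practices, the fractional covariate is delayed by an additional 6 months relative to the Series implementation scheme", because "one pair of targets (blood pressure/smoking or aspirin/cholesterol) is delayed by 6 months in each practice". Data generated this way were analysed by logistic GEE, and Table 3 reports >95% power for every ABCS endpoint. The section does not say which exposure coding that GEE fitted.

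Analysis (Analytic plan). In the paragraph on capacity to change, "The exposure of interest will be a dummy variable indicating the implementation support strategy exposure", coded by randomized assignment under intention to treat. The same paragraph says that time since initiation and its interaction with support will be considered, to look for a delayed effect. If the interaction is significant, analyses are stratified by time period. Secular trends will also be considered. The next paragraph, on ABCS, specifies a patient-level logistic model and restates no exposure coding.

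Order of targets (Evaluation design). Within each wave, "half of the counties introduced blood pressure management and smoking cessation support first and the other half introduced aspirin use and cholesterol management first". The power section describes the delay by practice.

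**The concern.** The exposure term behind the power figure and the one named for analysis are different variables. If the effect grows over a year, a single 0/1 term gives early, weak exposure the same weight as full exposure. If it also switches on at wave start, two of the four targets count as exposed for 6 months before they are introduced.

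In a stepped wedge with calendar-quarter effects there is a further cost. Practices that have already started, and whose effect is still growing, serve as comparators for later starters, which pulls the coefficient below a simple average of the effect. At stake are the size of the reported ABCS effect and whether Table 3 describes the test that will be run.

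**Working it through.** **Inputs from the protocol.** 263 practices; 11 quarterly time points; 4 waves; ramp 0.25/0.5/0.75/1.0; delay of 6 months (2 quarters) for half the practices on each target; within-practice correlation of at most 0.10; two-sided alpha of 0.05; blood pressure 65% to 70%, aspirin and smoking 60% to 70%, cholesterol 15% to 25%.

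**Assumed.** Equal waves; 20-100 patients per practice-quarter (m); correlation ρ of 0.02-0.10; waves 3 or 6 months apart (Fig. 4 is not shown); no dropout.

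**Set-up.** With wave start s and delay d (0 or 2 quarters), the true effect in quarter t is f = min(1, max(0, 0.25 × (t − s − d + 1))) of the 12-month effect. The wave-start dummy is 1 when t ≥ s, and the target-start dummy is 1 when t ≥ s + d. Practice-quarter means have covariance V = p(1−p)[ρ·(matrix of ones) + ((1−ρ)/m)·(identity)]. X holds 11 quarter indicators and one exposure term. The expected coefficient is the last element of (ΣX′V⁻¹X)⁻¹ΣX′V⁻¹f. With z = coefficient × 0.05 / SE for blood pressure, power = Φ(z − 1.96) + Φ(−z − 1.96).

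**The plan's own figure.** It cannot be reproduced exactly, because patients per quarter, the error variance and Fig. 4 are not available. With matched fractional coding, ρ = 0.10 and 3-month waves, blood-pressure power is 54% at m = 5, 97.6% at m = 20 and >99.9% at m = 50. The stated >95% is therefore plausible for matched coding.

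**One case in full** (ρ = 0.10, m = 20, 3-month waves, p = 0.675):

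- Fractional: 1.00 × 0.05 / 0.0127 = 3.94, power 97.6%.
- Target-start dummy: 0.288 × 0.05 / 0.0076 = 1.89, power 47%.
- Wave-start dummy: 0.031 × 0.05 / 0.0085 = 0.18, power 5%.

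**Ranges over ρ and m, blood pressure:**

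| Exposure term | Wave spacing | Share of 12-month effect | Power |
|---|---|---|---|
| Wave-start dummy | 3 months | 2-6% | 5-7% |
| Wave-start dummy | 6 months | 6-15% | 9-24% |
| Target-start dummy | 3 months | 28-32% | 47-98% |
| Target-start dummy | 6 months | 37-44% | 82% to >99% |
| Fractional covariate | either | 100% | at least 97% |

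The upper ends depend on when the first wave starts. With 6-month spacing and a first wave one quarter later, the shares reach 16% and 45%, and the wave-start power reaches 35% (0.100 × 0.05 / 0.0032 = 1.56).

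**Where the shrinkage comes from.** The simple mean of the ramp over wave-start exposed practice-quarters is 0.55-0.82. The rest of the loss comes from how the estimator weights early exposure once calendar quarters are in the model.

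**Logistic GEE check** (300 data sets per scenario, exchangeable working correlation, m = 20 or 50). With the wave-start dummy, power is 4-10% for blood pressure, 9-22% for 60% to 70% and 8-37% for cholesterol. With the target-start dummy, blood-pressure power is 37-78% (3-month waves) or 82% (6-month), and the 10-point endpoints have 86-100%. With the fractional covariate, power is 94-100%. Some scenarios include extra practice-by-quarter variance; with it, the target-start blood-pressure power in the first calculation can fall to 35%.

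**Without calendar-quarter effects.** Power is about 100%, but the estimate is 49-63% of the 12-month effect (wave start) or 61-72% (target start), and nothing protects it from secular trend.

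**The time-since-initiation provision.** Let D be the dummy and E the time since initiation, set to 0 before exposure. Then E × D = E, so the main effect and the interaction are the same column and cannot be estimated separately. With D plus one slope in E, timed from wave start, the slope is significant for blood pressure in 34-66% of data sets (3-month waves) or 95% (6-month), and for the 10-point endpoints in 82-100%.

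**The case against.** Four points deserve weight.

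1. The dummy sentence concerns capacity-to-change outcomes. That is correct, and its use for ABCS is an inference. It is a strong one: the parent goal covers capacity, performance and patient outcomes together, no other coding is given, and the same paragraph relies on 11 time points although the surveys have three.
2. Both wave and target order were randomized, so coding by randomized assignment can equally mean each target's own start. The text does not exclude this. On that reading the attenuation remains, but power is much better.
3. The plan foresees a delayed effect. It does, but the terms are only to be considered, act only after a significance test, are not separately estimable and do not address the target-specific delay. If the stratification is by calendar period, no unexposed practices remain once all waves have started.
4. Calendar-quarter effects are not fixed in the analysis, and without them power survives. The price is confounding with secular trend, which the plan itself raises.

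A reader might infer that an effective programme would most likely be reported as having no effect and that the >95% is lost for every ABCS endpoint. The documents do not support this. It needs the wave-start reading, calendar-quarter effects, and disregard of the time-since-initiation terms, none of which is fixed.

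**Conclusion.** The mismatch is real and stands in the text: the effect pattern used for power is a delayed ramp, the only exposure term named for analysis is a 0/1 dummy, and Table 3 cannot be assumed to describe the latter. With calendar-quarter effects and exchangeable correlation, the dummy recovers about 2-15% of the 12-month effect from wave start (blood-pressure power about 5-24%) or about 28-44% from target start (about 47% to over 99%), where the 10-point endpoints can keep >95%. Every dummy variant with quarter effects stays below half of the effect that Table 3 assumes. The figures rest on the assumed patient counts, correlation and wave spacing, and on the plan's own ramp being true. What the documents leave open, namely the exposure term for ABCS and the date on which it starts, moves blood-pressure power from about 5% to over 95%.

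**What to change.** For each ABCS target, prespecify exposure timed from that target's randomized start (wave start plus 0 or 6 months) and include calendar-quarter effects. In place of the single dummy, use either the fractional covariate from the power model or indicators for time since that target's start. Both follow randomized assignment, so intention to treat is kept. State which coefficient is the main ABCS estimate.

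State which coding the GEE behind Table 3 fitted and, if it was not this one, re-simulate the power under the model to be used. Reconcile whether target order was assigned by county (Evaluation design) or by practice (power section), because the exposure variable is built from it.

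The cost is wording, a few lines of code and possibly one simulation. Indicators free the analysis from the assumed linear ramp, at a standard error for the 12-month effect about 4-5% larger (0.0135 against 0.0129 at 20 patients per practice-quarter).
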